### **1.27 Criteria for Causal Relationship to the Trial Fluid**

Adverse events that fall under either "Possible" or "Probable" will be defined as "adverse events whose relationship to the Trial Fluid could not be ruled out".

### **1.28 Criteria for Defining the Severity of an Adverse Event**

Severity of AEs will be graded according to Common Terminology Criteria for Adverse Events Version. The following guidelines will be used to determine grade:

**Table 10: Criteria for Defining the Severity of a Trial Fluid Adverse Event Grade Description**

| Grade | Symptoms                                                                                                                                                                                           |
|--------------|-----------------------------------------------------------------------------------------------------------------------------------------------------------------------------------------------------------|
| 1     | Mild ; asymptomatic or mild symptoms, clinical or diagnostic observations only; and intervention not indicated.                                                                                    |
| 2     | Moderate ; minimal, local or non-invasive intervention indicated; limiting age; and appropriate instrumental activities of daily living.                                                           |
| 3     | Severe or medically significant but not immediately life-threatening ; hospitalization or prolongation or hospitalization indicated; disabling; and limiting self-care activities of daily living. |
| 4     | Life-threatening consequences ; and urgent intervention indicated.                                                                                                                                 |
| 5     | Death related to AE.                                                                                                                                                                               |

## STATISTICAL CONSIDERATIONS

### 1.29 Power calculations and sample size

A recently published open label sequential period study of chloride-liberal vs. chloride-restrictive fluid administration demonstrated a reduction in the incidence of injury and failure based on RIFLE criteria from 14% (95% CI, 11% - 16%) to 8.4% (95% CI, 6.4% - 10%);  $P < 0.001$ ) with the introduction of a chloride-restrictive fluid regime.

Assuming that, as we have conservatively estimated, we can study 2000 subjects over a 24 week period, our sample size will provide more than 80% power with an alpha of 0.01 to detect a difference of this magnitude.

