## BACKGROUND AND RATIONALE

For all patients undergoing major surgery, two important and fundamental goals in fluid intervention include the maintenance of intravascular volume to ensure optimal organ perfusion and function, and the avoidance of metabolic and electrolyte disturbances that can compromise organ function.

Worldwide, the most commonly used crystalloid fluids available for all patients undergoing surgery include:

1. Balanced solutions, commonly Plasmalyte solution or Hartmann's solution
2. Saline (0.9%)

The electrolyte composition of some of these commonly used crystalloid fluids are summarised in Table 1. All these solutions have similar sodium concentrations (130-150 mmol/L) and may contain physiological concentrations of potassium (Hartmann's and Plasmalyte solutions). There are however some major differences in anion composition. All three solutions above have chloride as a major anionic constituent, the balance in Hartmann's and Plasmalyte solutions being made up of lactate and acetate respectively. Both lactate and acetate are ultimately metabolised by the liver to bicarbonate, thus producing a near ideal physiological solution. Because their electrolyte composition is similar to plasma, they are frequently called "balanced" crystalloid solutions.

Pre-clinical and early clinical data suggest the saline may give rise to adverse effects including immune dysfunction, gastrointestinal dysfunction and decreased renal cortical perfusion and renal blood flow. There is strong expert opinion that 'normal saline' or saline(0.9%) is neither "normal" nor "physiological". In fact, it has approximately 1.5 times more chloride than normal plasma and its use can lead to hyperchloraemic acidosis. Although hyperchloraemic acidosis may be a benign phenomenon, recent data raise the possibility that the use of saline for fluid resuscitation in adult ICU patients may lead to an increased risk of developing acute kidney injury compared to resuscitation fluids with a lower concentration of chloride such as Plasmalyte.

In a single centre prospective open-label sequential period pilot study of 1533 critically ill patients, the implementation of a chloride-restrictive strategy that included avoiding the use of normal saline was associated with a significant decrease in the incidence of acute kidney injury and use of renal replacement

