### 1.11 Summary

The demographic, illness severity and outcome data that will account for the majority of data used in this study are already being collected. Existing data suggest that our study will have ample statistical power to establish whether using saline as the default resuscitation fluid increases the risk of acute kidney injury in adult major surgery patients compared to Plasmalyte. The statistical team at the Australian and New Zealand Intensive Care Research Centre, who will conduct the statistical analyses, are familiar with the data being used in the study.

Baxter Pty will provide blinded study fluids for this study. In short, this study has a very high chance of success. It should provide high quality pilot data for a subsequent pivotal, NHMRC-funded, double-blind randomized multicentre pragmatic interventional trial that will inform clinical practice around the world.

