### 1.13 Inclusion criteria

- Patients aged  $\geq 18$  years admitted to the Austin Hospital who receive major surgery. For the purpose of the study, major surgery will be defined as any surgery requiring overnight post-operative hospital stay.

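### The power in section 1.29 rests on event rates from critically ill patients, so the claim of ample power in overnight-stay surgical patients (section 1.11) is unsupported

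*Protocol*

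**What the plan says.** Section 1.29 of the protocol takes its planning rates from one published open-label sequential-period study, which "demonstrated a reduction in the incidence of injury and failure based on RIFLE criteria from 14" per cent "to 8.4% (95% CI, 6.4% - 10" per cent). It assumes that "we can study 2000 subjects over a 24 week period" and concludes that "our sample size will provide more than 80% power with an alpha of 0.01 to detect a difference of this magnitude". It does not say who was studied. Section 1.10 gives the split as about 1000 per group.

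The Background and Rationale section describes the same reference: "In a single centre prospective open-label sequential period pilot study of 1533 critically ill patients".

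The population of this trial is set in section 1.13, where "major surgery will be defined as any surgery requiring overnight post-operative hospital stay". The synopsis admits elective and emergency operations, and section 1.31 lists orthopaedics and urology among the surgery types. ICU admission is not an entry condition. It is a secondary outcome in 1.17.3, and section 1.15 collects APACHE data only from those who reach the ICU.

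Section 1.11 says: "Existing data suggest that our study will have ample statistical power". The rest of that sentence applies the claim to adult major surgery patients.

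**The concern.** The only event rates behind the power statement come from a population that the trial does not select for. Nowhere does the protocol give a RIFLE injury or failure rate for surgical patients, at this hospital or elsewhere. The retrospective abdominal-surgery study in the background is cited without rates. No reason is offered for carrying the ICU rates across, and no other rate is tried.

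The power of a two-proportion comparison at a fixed relative effect depends strongly on the control rate. If overnight-stay surgical patients have a lower rate than ICU patients, the same relative effect is harder to detect with 2000 patients. A reader of 1.11 would take the trial as well powered for its primary outcome in its own population, and would weigh a non-significant result accordingly when deciding whether a pivotal trial is justified.

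The protocol also pulls in two directions. Section 1.6 and the Background and Rationale section say that pilot data are needed for power calculations in this setting, while 1.11 says existing data already show ample power.

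**Working it through.** **Inputs from the protocol.** Control rate 14% and comparison rate 8.4% (1.29), so the relative risk is 0.084 / 0.14 = 0.60 and the difference is 5.6 points. Alpha 0.01 and more than 80% power (1.29). 1000 per group (1.10). Unadjusted chi-square test (1.30).

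**Inputs assumed.** Two-sided test, as the protocol does not state sidedness. No dropout, as no allowance is stated. Patients treated as independent.

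**Formula.** With n per arm, p̄ = (p1 + p2)/2 and Φ the standard normal distribution function:

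power = Φ{ [ |p1 − p2| − z·√(2p̄(1 − p̄)/n) ] / √( [p1(1 − p1) + p2(1 − p2)]/n ) }, with z = 2.576 at alpha 0.01 and 1.960 at alpha 0.05.

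**Step 1: reproduce the plan's figure.** p1 = 0.14, p2 = 0.084, p̄ = 0.112, n = 1000.
- Null standard error: √(2 × 0.112 × 0.888 / 1000) = 0.01410
- Alternative standard error: √((0.1204 + 0.0769)/1000) = 0.01405
- (0.056 − 2.576 × 0.01410) / 0.01405 = 1.40, so power = 92%

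One-sided, it is 95%. The size needed for 80% power, two-sided, is 740 per arm (775 with continuity correction), below 1000. The statement in 1.29 is correct for its inputs.

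**Step 2: keep the relative risk at 0.60 and vary the control rate.** Example at 5% versus 3%, with p̄ = 0.04:
- Null standard error: √(2 × 0.04 × 0.96 / 1000) = 0.00876
- Alternative standard error: √((0.0475 + 0.0291)/1000) = 0.00875
- Alpha 0.01: (0.02 − 2.576 × 0.00876) / 0.00875 = −0.29, so power = 38%
- Alpha 0.05: (0.02 − 1.960 × 0.00876) / 0.00875 = 0.32, so power = 63%

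| Control rate | Comparison rate | Power, alpha 0.01 | Power, alpha 0.05 |
|---|---|---|---|
| 14% (source study) | 8.4% | 92% | 98% |
| 11% (lower limit of the source interval) | 6.6% | 82% | 94% |
| 10% (assumed) | 6.0% | 77% | 91% |
| 8% (assumed) | 4.8% | 64% | 83% |
| 5% (assumed) | 3.0% | 38% | 63% |
| 3% (assumed) | 1.8% | 21% | 42% |

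**Step 3: the control rate at which power is 80%.** Solving the formula with p2 = 0.6 × p1 and n = 1000 gives about 10.7% at alpha 0.01 and about 7.4% at alpha 0.05.

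**Step 4: the other reading of the planned difference.** If the difference meant is the absolute 5.6 points, power stays high at lower control rates: 10% versus 4.4% gives 99% at alpha 0.01. The relative reduction this requires grows: 5.6/10 = 56%, 5.6/8 = 70%, 5.6/6 = 93%. Below a control rate of 5.6% it cannot occur. The documents give no basis for relative effects larger than the source study's 40%.

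**The case against.** Several points on the other side stand:

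- Section 1.29 contains no false statement. Its power is correct for the rates it quotes, and its source can be traced through the reference number to the background section and the reference list.
- Every control rate below the source study's figures is an assumption. At 11%, the lower limit of the source's own interval, power at alpha 0.01 is still 82%.
- Section 1.30 reports relative risks with 95% confidence intervals and does not carry the 0.01 level into the test. At alpha 0.05 power is 83% at a control rate of 8%, so the stricter level should not be shown alone.
- This is a pilot sized by theatre workload (1.10), and outcome data for later power calculations are among its stated products.
- A local rate may not be easy to obtain. Section 1.21 lists the renal-outcome data among the few items not routinely collected for quality assurance, although 1.7 and 1.15 describe the study data, including baseline creatinine, as routine.

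These points limit the concern but do not answer it. Pilot status does not support a claim of ample power to establish an effect on kidney injury. A source that can be traced is not a reason for applying its rates to a different population.

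A reader might infer that the trial is underpowered. The documents do not support that, because they give no surgical rate. A reader might also expect a rule that a non-significant result be called inconclusive. That is reporting text which can be left to the statistical analysis plan.

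**Conclusion.** The power figure in 1.29 is arithmetically correct but applies to critically ill patients. The claim of ample power for adult major surgery patients in 1.11 has no support in the protocol. It is unsupported, not shown to be false.

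In size, the more-than-80% statement holds for this trial only if the control rate is at least about 10.7% at two-sided alpha 0.01, or 7.4% at alpha 0.05. Over assumed control rates from 10% down to 3%, power runs from 77% to 21% at alpha 0.01 and from 91% to 42% at alpha 0.05.

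This rests on a relative reduction of 40%, 1000 evaluable patients per arm, a two-sided test, and independent patients. Allocation by 6-week block (1.17) is a separate matter that these figures do not account for. The point should be corrected, but it does not call for a change in sample size.

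**What to change.** In section 1.29, state that the source study enrolled critically ill patients, and replace the single power statement with a conditional one. Possible wording:

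> The planning rates come from critically ill adults; the corresponding rate in patients staying overnight after surgery is not known. With 1000 patients per group and a 40% relative reduction, power at two-sided alpha 0.01 (0.05) is 92% (98%) if the control rate is 14%, 77% (91%) at 10%, 64% (83%) at 8%, 38% (63%) at 5% and 21% (42%) at 3%. Power of 80% requires a control rate of at least about 10.7% (7.4%).

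If a RIFLE injury or failure rate for overnight-stay surgical patients can be derived from existing creatinine records, add power at that rate. In section 1.11, delete the word ample, or qualify the claim with the control rate it requires.

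The cost is one rewritten paragraph and one edited sentence. Deriving a local rate is extra work, and given section 1.21 it may take more than a single data query. The sample size and conduct do not change. The downside is a less favourable stated power.

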### 1.30 Analysis plan

A complete description of the statistical analyses will be specified in a statistical analyses plan, finalised prior to completion of the study.

All analyses will be conducted on an intention-to-treat basis.

The primary analyses will be unadjusted analyses in which binary outcomes will be compared using relative risks with 95% confidence intervals and chi square tests and continuous outcomes will be compared with the use of mean

**The SPLIT Study: Saline (0.9%) vs. Plasma-Lyte® 148 Fluid Intervention  
Trial in Major Surgery Patients, Version 3, 1st Oct 2014**

differences and un-paired T-tests assuming that normality assumptions are met. If normality assumptions are not met then we plan to attempt simple data transformation, such as a logarithm transformation, and if this fails to proceed to a Mann-Whitney rank based test. Adjusted analyses will be performed using Poisson regression for binary outcomes and linear regression for continuous outcomes. Baseline covariates will include age, gender, elective vs. emergency surgery, surgical specialty of admission, type of operation, and baseline serum creatinine level. Survival times will be compared using log-rank tests and presented as Kaplan-Meier curves.

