| Statistical Methods:        | 
A complete description of the statistical analyses will be specified in a statistical analyses plan, finalised prior to completion of the study.
 
All analyses will be conducted on an intention-to-treat basis.
 
Primary analyses: will be unadjusted analyses in which binary outcomes will be compared using relative risks with 95% confidence intervals and chi square tests and continuous outcomes will be compared with the use of mean differences and unpaired T-tests assuming that normality assumptions are met.
 
If normality assumptions data transformation will be attempted, such as a logarithm transformation, and if this fails to proceed to a Mann-Whitney rank based test.
 
Adjusted analyses: will be performed using Poisson regression for binary outcomes and linear regression for continuous outcomes. Baseline covariates will include age, gender, elective vs.
 |

**The SPLIT Study: Saline (0.9%) vs. Plasma-Lyte® 148 Fluid Intervention Trial in Major Surgery Patients, Version 3, 1st Oct 2014**

|                   |                                                                                                                                                                                                                                    |
|-------------------|------------------------------------------------------------------------------------------------------------------------------------------------------------------------------------------------------------------------------------|
|                   | emergency surgery, surgical specialty of admission, type of operation, and baseline serum creatinine level. Survival times will be compared using log-rank tests and presented as Kaplan-Meier curves.                             |
| Subgroups: | Patients undergoing abdominal surgery
Patients undergoing vascular surgery
Patients undergoing thoracic surgery
Patients undergoing other surgeries (orthopaedics, urology etc.)
Patients undergoing emergency surgery |

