### 1.15 Baseline data

The following baseline data will be collected:

- Age
- Gender
- Admission type (elective vs. emergency)
- Type of surgery (hepatobiliary, colorectal, upper GI, orthopaedic etc.)
- If admitted to ICU: Chronic APACHE co-morbidities (including long-term dialysis)
- If admitted to ICU: APACHE-III admission diagnosis
- If admitted to ICU: Illness severity based on the on the APACHE-III risk of death score
- Baseline creatinine.
- Baseline biochemistry

**(Note: - all of these data are routinely collected for quality assurance purposes or as measured as part of usual clinical care)**

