### 1.17.3 Secondary outcome measures

Secondary outcomes will be

- the incidence of acute kidney injury based on creatinine according to risk, injury, failure, loss, end-stage (RIFLE) classification in the first 3 days hours after surgery,
- the increase between baseline and peak chloride levels in the first 3 days after surgery
- the development of metabolic acidosis (defined as a base deficit > 2 mEq/L or a bicarbonate level <20 mmol/L) in the first 3 days after surgery
- the development of acidemia defined as a pH <7.3 in the first 3 days after surgery
- Postoperative complications
- Need for and duration of renal replacement therapy,
- Proportion of patients requiring mechanical ventilation
- Need for ICU admission
- ICU and hospital length of stay, and
- ICU and in-hospital mortality

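### The covariates named for the adjusted analyses omit baseline acid-base status, and the acidosis and acidaemia outcomes do not say how patients already past the threshold are counted

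*Protocol*

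**What the plan says.** Section 1.30 makes the unadjusted comparison primary: "The primary analyses will be unadjusted analyses in which binary outcomes will be compared using relative risks". The adjusted analyses come second: "Adjusted analyses will be performed using Poisson regression for binary outcomes and linear regression for continuous outcomes". One covariate list follows for both model types: "Baseline covariates will include age, gender, elective vs. emergency surgery, surgical specialty of admission, type of operation, and baseline serum creatinine level". The synopsis gives the same list, ending "surgical specialty of admission, type of operation, and baseline serum creatinine level". No covariate is tied to a particular outcome. Section 1.30 also leaves the detail to a separate document: "A complete description of the statistical analyses will be specified in a statistical analyses plan, finalised prior to completion of the study".

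The Objectives section puts biochemical and acid-base derangement second among the specific aims, after kidney injury. Section 1.17.3 turns this into two binary secondary outcomes, both in the first three days after surgery. One is "the development of metabolic acidosis (defined as a base deficit > 2 mEq/L or a bicarbonate level <20 mmol/L"; the other is a pH below 7.3. The same list measures chloride as a rise from baseline to peak.

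Section 1.15 collects "Baseline biochemistry" without listing its components. Emergency surgery is eligible (synopsis), and acidosis before surgery is not an exclusion (section 1.14). Sections 1.17 and 1.19 set the fluid by calendar period, with one six-week block for each.

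**The concern.** The named list suits the renal outcome, because baseline creatinine is the starting value of the quantity that defines kidney injury. It contains no matching value for the acid-base outcomes, although bicarbonate, base deficit or pH before surgery is the starting value of what they measure.

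Two separate issues follow.

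- **Covariate.** With one block per fluid, the allocation does not balance patients individually, so adjustment is the main analytic protection against a change in case mix. If patients in one block arrive somewhat more acidotic, the urgency and specialty terms capture that only in part. The rest appears as a fluid effect. Leaving out the baseline value also costs some precision.
- **Counting rule.** A patient who arrives with bicarbonate below 20 mmol/L meets the written threshold whichever fluid is given. If such patients are counted equally in both blocks, they pull the relative risk towards 1. If they are more common in one block, they bias it.

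The Background section cites hyperchloraemic acidosis as a known consequence of saline, so these outcomes are likely to be read closely when the pivotal trial is planned.

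**Working it through.** **The plan's own figure.** The only power statement is for the primary outcome (section 1.29): 14% versus 8.4%, alpha 0.01, 2000 patients. With 1000 per group, the two-proportion calculation gives 92% power two-sided, so the stated figure of more than 80% reproduces. It says nothing about acidosis. The protocol gives no acidosis rate before or after surgery, so every rate below is assumed.

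**A. Counting rule.** Let b be the share already past the threshold, all counted as events, and q the new-onset rate in the rest. The counted rate is P = b + (1 − b)q.

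True new-onset rates of 30% and 20% (RR 1.50), same b in both blocks:

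| b | P in block 1 | P in block 2 | RR |
|---|---|---|---|
| 5% | 0.335 | 0.240 | 1.40 |
| 10% | 0.370 | 0.280 | 1.32 |
| 20% | 0.440 | 0.360 | 1.22 |
| 30% | 0.510 | 0.440 | 1.16 |

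At b = 20%, power (1000 per group, alpha 0.05 two-sided) is 0.955 with prevalent cases counted and 0.996 with them excluded. For a rarer outcome, with 14% and 8.4% as stand-in rates (true RR 1.67), the RR falls to 1.29 at b = 10% and 1.17 at b = 20%. Power is then 0.804 and 0.598, against 0.965 and 0.945 with exclusion.

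No fluid effect (q = 20% in both blocks), unequal b:

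- 12% versus 8%: 0.296 / 0.264 = 1.12.
- 15% versus 10%: 0.320 / 0.280 = 1.14.

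**B. Covariate.** Simulation of the bicarbonate limb only, 1000 trials per scenario. Assumed inputs: 1000 patients per block; 30% emergency; baseline bicarbonate mean 25 mmol/L (23.5 for emergencies), SD 3; mean nadir 2 mmol/L lower; event = nadir below 20, about 20% of patients; baseline-to-nadir correlation 0.4 to 0.75. The model was Poisson with robust standard errors, adjusted for urgency and age only.

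- Of the events, 17% to 28% were already below 20 at baseline.
- No fluid effect, baseline 0.3 mmol/L lower in one block: false RR 1.05 to 1.11, rejection at the 5% level in 10% to 21% of trials. Adding baseline bicarbonate returned rejection to 5% to 6.5%.
- The same with 0.5 mmol/L: rejection in 16% to 51%.
- No imbalance, true RR 1.19: power rose from about 57% to between 62% and 66%.

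A repeat with 600 trials per scenario agreed on the bias (RR 1.05 to 1.10, rejection 8% to 21%, back to 4% to 5% with the covariate). It gave a slightly smaller power gain (55–59% to 58–64%).

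Closed-form check, taking nadir SD 3. Without a shift the event rate is 0.7 × Φ(−1) + 0.3 × Φ(−0.5) = 0.7 × 0.1587 + 0.3 × 0.3085 = 0.2036. A 0.3 mmol/L baseline shift moves the nadir by correlation × 0.3.

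- Correlation 0.4, nadir shift 0.12: 0.7 × Φ(−0.96) + 0.3 × Φ(−0.46) = 0.2148; RR 0.2148 / 0.2036 = 1.05.
- Correlation 0.75, nadir shift 0.225: 0.7 × Φ(−0.925) + 0.3 × Φ(−0.425) = 0.2249; RR 0.2249 / 0.2036 = 1.10.

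**How large a shift is 0.3?** The standard error of the block difference is 3 × √(2/1000) = 0.134 mmol/L. So 0.3 is 2.2 standard errors and 0.5 is 3.7. Chance alone would seldom produce either; they stand for a systematic change in case mix between blocks.

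**The case against.** The strongest objection is that this belongs in the statistical analysis plan, which is not at hand. The protocol says what the covariates will include, which is not an exhaustive list, and it promises a full description later. A reader might infer that the list is closed and that bicarbonate can never be adjusted for. The text does not support that. What stands is narrower: the protocol does name a list, and that list fits one outcome and not these two.

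A reader might also infer that patients acidotic on arrival will certainly be counted as fluid events. That goes too far as well. Section 1.17.3 speaks of the *development* of acidosis and acidaemia, which can mean new onset. Read literally, the thresholds would count such patients; read for intent, they might not. The defect is the ambiguity.

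Three further objections are fair.

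- A covariate does not change who counts as an event and leaves the unadjusted primary comparison as it is. The two issues need two remedies.
- The simulation omits gender, specialty, operation type and creatinine, all of which are planned and some of which could absorb part of a case-mix difference. It models neither the base-deficit limb nor acidaemia. Its results do not measure the bias left by the full planned model.
- Section 1.15 does not name bicarbonate. A postoperative cut at 20 mmol/L does not prove that a value before surgery is available for everyone.

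These limit the size and certainty of the point. They do not answer why the baseline value of the measured quantity is missing from the named list.

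**Conclusion.** The point holds as a low-cost improvement to secondary outcomes. The named covariates contain creatinine and no acid-base value, and the two threshold outcomes lack a stated baseline rule, although chloride in the same list has one. With one block per fluid, a difference in acid-base status on arrival can pass into the adjusted relative risk. Prevalent cases balanced across blocks dilute that relative risk.

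The size is illustrative only. A false relative risk of about 1.05 to 1.11 needs an assumed 0.3 mmol/L shift in baseline bicarbonate, and dilution from 1.50 to between 1.22 and 1.32 needs an assumed 10% to 20% prevalence. The documents supply neither figure and give no evidence that the blocks differ. The kidney injury outcome and its power are unaffected. Adjustment for one covariate also does not cure the wider weakness of having a single period per fluid.

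**What to change.** Add to section 1.30 and the synopsis: *Adjusted models for metabolic acidosis and acidaemia also include baseline bicarbonate (continuous) from the baseline biochemistry, where measured. For both outcomes, unadjusted and adjusted results are also shown excluding patients who already met the outcome definition at baseline.* Keep creatinine in the list.

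The first sentence deals with the covariate and the second with counting, so the unadjusted primary comparison is covered too.

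The cost is two sentences and one variable expected to lie within data already collected. A rule is needed for patients without a baseline bicarbonate, such as imputation or a missing-value category. Bicarbonate is only a partial proxy for baseline pH or base deficit, so adjustment for acidaemia and for the base-deficit limb will be incomplete. Some patients may also lack the values needed to judge whether they met the definition at baseline, and the number should be reported.
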